#### Randomization

A cluster-randomized design was chosen over individual patient randomization in order to avoid intervention contamination and logistic complications within the GP offices. Participating GP offices are randomly assigned to either the intervention or the control arm. To prevent foreknowledge of treatment assignment, the allocation of the practices to the study arms will be concealed from research staff, GPs, and CMs until the intervention process is activated in the intervention arm: after obtaining written consent from participating GPs, a research assistant generates a pseudonymized code for each practice and submits this code to an independent statistician at the Department of Medical Psychology in Hamburg. Participating practices are then assigned to the intervention or control group with a 1:1 ratio according to a computer-generated randomization schedule prepared by the statistician (STATA 12.1, procedure ralloc). Block randomization is used with three variable block sizes, with randomization stratified by site. After assignment to the intervention or control group, the pseudonymized practice identifiers and the study arm allocation are returned to the research assistant at the respective study site. This information is then used to enable intervention activation at practices in the intervention arm. The randomization schedule for the two sites, including the pseudonymized codes for the practices and their assignment, remains with the statistician. Study objectives, intervention, and data assessment pertain to the individual patient level.

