### Blinding

Since there is no placebo condition, blinding after assignment is impossible. However, patients in the intervention and control groups only receive information pertaining to their respective study arm so that each group is unaware of the condition of the other group. In both groups, patient outcomes are collected by the data management team (assessors) to prevent the involvement of the CM in patient assessment. The assessors will contact patients in both study arms repeatedly to ensure a low rate of missing data. Due to the pseudonymization process, the statistician will, at all times, be unaware of the identity of the participating practices. Moreover, the statistician will analyze the primary and secondary outcome data without knowledge of the subjects’ allocation to the study arms. For additional analyses of the treatment process, this kind of blinding is not possible.

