**Intervention group only**					
Evaluation of intervention	–		–		X
Therapy preference questionnaire	X		–		–
Depression (PHQ-9) - additional measures	–	each session	–	each session	–

*Primary time of assessment (t_**2**_) after intervention.

**Linguistic and culture-specific modifications

*Abbreviations:* PHQ-9, the Patient Health Questionnaire; CDI, the Comorbidity Disease Index; GAD-7, the seven-item Generalized Anxiety Disorder Scale; CPG, the Graded Chronic Pain Scale; FIMA, Fragebogen zur Inanspruchnahme medizinischer und nicht-medizinischer Versorgungsleistungen im Alter; EQ-5D, EuroQol Group; RS-13, the 13-item Resilience Scale.

To avoid the loss of data at baseline and follow-up assessments, the assessors will contact patients whose questionnaires are missing by phone in intervals of 10 to 14 days. For patients who choose to discontinue the trial or deviate from the intervention protocol, a final telephone survey will be conducted. The follow-up calls by the assessors follow a standard operation procedure (SOP) that was defined to ensure a structured and systematic procedure in terms of subsequent collection of missing data via telephone. This approach is restricted to items that do not relate to the patient’s psychological background, with the exception of the PHQ-9 as primary outcome. If answers to more than one item in the PHQ-9 are missing, the PHQ-9 will be reassessed completely by the data management team (in this case, other data regarding health status will be declared invalid). Any revision has to be signed by the assessor with their name and date. Only completed questionnaires will be passed on to data entry.

According to the SOP, data will be entered corresponding to the defined coding plan in the EpiData Entry Client (Version 1.4.2; EpiData Manager Version 1.4.2 for data export) [46]. Instead of running a double data entry procedure, the entered data will be completely (100%) checked and, if necessary, corrected by a second person on the data management team. Data export files (Stata Version 12.1 and SPSS Statistics Version 21 [33, 47]) from both study centers will be centrally collected at the study center in Hamburg for statistical analysis.

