As after assignment the research stuff is not blinded, no external data monitoring committee is needed, and data concerning patient safety and treatment efficacy can be monitored internally. Similarly, auditing of the trial conduct will be administered by the research staff: the data management teams in Freiburg and Hamburg will monitor the completion of the questionnaires, while the study coordinators will ensure adherence to the intervention protocol.

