### Statistical analysis

The primary analysis will compare the proportion of patients remitted of depressive symptoms at the 12-month follow-up using a mixed-effects logistic regression model in the intention-to-treat sample (including all randomized patients). Treatment condition (intervention versus control) will be treated as a fixed effect. Baseline severity of depressive symptoms will be included as a covariate and variation among patient clusters (treated by the same GPs) will be modeled through random effects. Further binary outcomes will be modeled correspondingly. Continuous outcomes will be analyzed according to the same scheme, but in linear rather than logistic regression models. Item-level missing data in psychometrically sound instruments will be treated in compliance with the corresponding manuals. If no recommendations are available, the expectation-maximization (EM) algorithm will be used to impute up to 30% of missing item responses. Unit-level missing data (patients not providing data for a whole measurement point due to dropping out of the study, for example) will be imputed via the EM algorithm using existing information from the baseline and 6-month follow-up assessments. Further secondary analyses will include analyses in the per-protocol (completer) sample to test the robustness of the primary findings. No interim analysis is planned. Before the start of the analysis, a detailed statistical analysis plan (SAP) will be prepared by the responsible statistician. Intervention-related data are stored and analyzed separately. All analyses will be computed using Stata 12.1. Figure 4 provides a detailed overview of the study design.

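### The statistician said to analyse blind also keeps the list of practice codes with their arms, and the article describes nothing that would keep that person blind

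*Protocol article*

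**What the plan says.** **Allocation.** In the Randomization section a research assistant creates a code for each consenting practice and "submits this code to an independent statistician at the Department of Medical Psychology in Hamburg". That statistician prepares the schedule and sends the codes and arms back to the sites. The section then states: "The randomization schedule for the two sites, including the pseudonymized codes for the practices and their assignment, remains with the statistician."

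**Blinding of the analysis.** The Blinding section says: "Due to the pseudonymization process, the statistician will, at all times, be unaware of the identity of the participating practices." The next sentence adds that "the statistician will analyze the primary and secondary outcome data without knowledge of the" patients' allocation. Only the additional analyses of the treatment process are exempted.

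**Outcome collection.** The same section opens: "Since there is no placebo condition, blinding after assignment is impossible." It assigns outcome collection to the data management team so that care managers take no part. The default is a mailed questionnaire (Assessment section). Missing data are pursued by telephone, and when more than one PHQ-9 item is blank, "the PHQ-9 will be reassessed completely by the data management team" (Assessment section, text after Table 2).

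**Monitoring.** The end of the Assessment section gives the unblinded research staff as the reason for having no external committee, and says that "data concerning patient safety and treatment efficacy can be monitored internally". The Statistical analysis section says: "No interim analysis is planned."

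**The concern.** Patients and providers know what care is given, and the primary outcome is self-reported. Masking the analyst and the staff who telephone patients are therefore the main safeguards left. The article claims the first, but describes an arrangement in which the person concerned holds the key to the arms. If that person can link the analysis file to the list, the remaining choices (SAP details, handling of missing data, sensitivity analyses) could be made with the arm known, while readers are told they were made blind.

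The second safeguard is dismissed on a reason that does not carry. The lack of a placebo prevents masking of patients and providers. It does not prevent masking of a person who telephones to complete a questionnaire.

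The permission to monitor efficacy internally leaves open who may see outcome data by arm before the end of the trial.

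**Working it through.** No figure in the article bears on this point, so the check is a comparison of its statements.

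**1. One statistician or two?** The Randomization section introduces a single independent statistician in Hamburg. The Blinding section uses the definite article and refers to the pseudonymization process, which is the one described under Randomization. Its sentence on blind analysis follows directly, joined by a word that continues the same subject. The Setting section places the statistical analysis in Hamburg too. The natural reading is one person. The Statistical analysis section speaks of a responsible statistician who writes the SAP, but does not say that this is someone else.

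**2. What does pseudonymization hide?** It replaces the practice name by a code. The retained list joins that code to an arm. Its holder does not know which practice a code stands for, but does know the arm of every code. Not knowing practice identity is therefore no evidence of not knowing allocation.

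**3. Can the list be linked to the analysis file?** The primary model has a random effect for patients of the same GP, so the file needs a cluster identifier.
- If the identifier is the randomization code, the arm follows at once by matching it to the list.
- If clusters are re-coded and the arm label is masked by someone else, that match is broken.

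The article does not say which applies. Blinding of the analyst is possible under the plan, but nothing described secures it.

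**4. Does the team that retakes the PHQ-9 know the arm?** Three statements indicate that it does:
- The Assessment section says that research staff are not blinded after assignment.
- The section on ethics and safety has the data management team screen questionnaires and document adverse events for control patients specifically. In the intervention arm the care manager documents adverse events.
- Table 2 lists two questionnaires for the intervention group only, so the returned forms can themselves show the arm.

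The retake falls under the telephone procedure, and the PHQ-9 is its named exception among psychological items. Remission is a cut-off (PHQ-9 below 5), so a small shift in answers can reclassify a patient.

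**5. Efficacy monitoring against no interim analysis.** The first statement permits internal monitoring of efficacy data without limiting it to individual safety review or to data pooled over arms. The second excludes an interim analysis. Both can be true only if the monitoring involves no comparison by arm, and the article does not say so.

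**The case against.** **On the analyst.** Re-coding clusters and masking the arm label are operational details that an article may leave to the SAP, and a SAP is promised before the analysis starts. The room for choice is also limited. The Statistical analysis section already fixes the intention-to-treat sample, the mixed logistic model, the baseline covariate, the cluster random effect and EM imputation. This stands in part. It narrows the harm, and it means that the analyst cannot be declared unblinded. It does not remove the conflict, because the article itself makes both statements and offers nothing to join them.

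**On the assessors.** A reader might infer that a stated blind is breached. It is not: the article claims only that assessors are separate from care managers, and says openly that staff are unblinded. The telephone retake is a fallback under a standard procedure. The article also cites evidence, in its description of the care manager contacts, that the PHQ-9 gives similar results by telephone. All of this stands, which is why the point is secondary. The cited evidence concerns mode, however, not a caller's knowledge of the arm.

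**On monitoring.** The wording is permissive and names no test, stopping rule or comparison. A reader might infer that efficacy by arm is examined when deciding whether to recruit more practices. The section on guaranteeing the sample size ties added practices to insufficient enrolment alone, so the document does not support that.

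**Conclusion.** The main point holds: the Randomization and Blinding sections conflict, and the stated blinding of the analyst is not secured. This assumes that both sections mean the same statistician, which is the natural reading but is not stated expressly. The stronger statement, that the analyst is in fact unblinded, goes beyond the article, because the content of the analysis file is not described.

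The assessor point holds as an unguarded route to bias in the primary outcome, confined to patients whose PHQ-9 is missing or incomplete. The monitoring point is an ambiguity to be reconciled, not evidence of an interim look.

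No size can be given. The effect of the analyst's knowledge cannot be quantified from the article. The effect of unmasked callers would be the share of outcomes taken by telephone times the change in remission among those patients, and the article gives neither. A reader might use the 15% in the Sample size section as that share. It is the assumed loss to follow-up, that is, the allowance for patients missing from the completer analysis. It is neither the telephone share nor an upper bound on it.

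The correction should be made because it is cheap and concerns a safeguard that the article claims. It requires no change to the design, sample size or treatment.

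**What to change.** 1. **Analyst.** Preferably, keep the schedule with a person who does not analyse, and say so. If one person must do both, someone else should supply the analysis file with new cluster identifiers and an A/B arm label, and without intervention-only variables. Unmask only after SAP sign-off and the primary run. The second option is weaker: if the arms differ in their number of practices, the list-holder could recognise them by counting. If neither is feasible, withdraw the claim of blind analysis. Cost: a reassignment of tasks or one data-preparation step.

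2. **Assessors.** Replace the statement that blinding is impossible with one limited to patients and providers. Where possible, have existing staff within each site make the PHQ-9 calls from a contact list without the arm. Record the mode of each PHQ-9 and repeat the primary analysis without those collected by telephone. Cost: some coordination of tasks. Some callers may still learn the arm from the patient, which should be acknowledged. Working within each site avoids moving contact data between centres.

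3. **Monitoring.** State that no outcome summaries by arm are produced before database lock. The review of individual questionnaires and events for safety is unaffected. Cost: one sentence.

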#### Recruitment of patients

Every participating GP is asked to screen his or her patients according to set inclusion and exclusion criteria and to include five patients for trial participation in the GP practice. Patients of the participating GPs who are 60 years of age or older and show moderate depressive symptoms in the scope of a diagnosed depressive episode, recurrent depressive disorder, or dysthymia (International Classification of Diseases, ICD-10, assessment) are eligible for enrollment at the individual level. Symptom severity is measured with the nine-item depression scale of the Patient Health Questionnaire (PHQ-9; inclusion score 10 to 14). Participants must be willing and able to be contacted regularly by the CM via telephone and to participate in a written survey.

For safety reasons and to avoid data contamination due to comorbidity effects, patients meeting any of the following exclusion criteria are excluded from study participation: alcohol or drug abuse, severe cognitive impairment (e.g., dementia), bipolar disorder, psychotic disorder or severe behavioral symptoms, obsessive compulsive disorder, suicidal ideation and other warning signs of suicide as well as active non-pharmacological (or combined) depression treatment by a specialist (e.g., a psychiatrist or psychotherapist) at time of inclusion. Before GPs apply the PHQ-9 questionnaire, potential participants receive oral and written information about the study. If patients agree to participate in the study, both GP and patient sign the informed consent sheet. Patients, GPs, and the corresponding local study center receive a copy of the signed documents. Subsequently, the local study center will send the baseline questionnaire to the patient. Completed questionnaires will be reviewed by the data management team at the local study centers with regard to exclusion criteria, plausibility of the answers, and completeness of the data.

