#### Strategy to guarantee the targeted sample size

In case of insufficient patient enrollment by the GPs, local study centers will recruit additional GPs who will be randomly allocated to one of the two study arms by the independent statistician (see above). Patients in the intervention group at each site will receive treatment as specified in the GermanIMPACT treatment plan manual. Patients in the control group at each site will receive treatment as usual (as agreed on with their GP without involvement of a CM and MHS). As the collaborative care approach was developed to support the treatment of depression in older adults in general practices, the comparison to a treatment-as-usual group was chosen to examine if ancillary care has an additional effect on symptom remission. This approach is analogous to the IMPACT study developed in the United States; since GermanIMPACT is an adaption of the original study, the same comparative conditions were chosen.

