### Training of GermanIMPACT care providers

The CMs receive comprehensive training by a psychologist familiar with the IMPACT concept and intervention techniques. They are provided with a detailed intervention manual to be used for further study and reference. Regular meetings with the trainers ensure the continuous high standard of the intervention. Clinical concerns are regularly discussed with the supervising MHS. All members of the GermanIMPACT study team are educated and instructed thoroughly in how to deal with emergencies, such as suicidal ideation.

Prior to participation, GPs are individually contacted by members of the study team and informed about the aims of the study and the nature and process of the intervention. Before the inclusion of the first patient, they are personally introduced to the CM assigned to their office.

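### Willingness to take care-manager calls cannot be asked of control patients, so as an inclusion criterion it in effect screens out refusers in intervention practices only

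*Protocol article*

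**What the plan says.** All references are to the protocol article.

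- **Recruitment of patients** states the criterion for participants in general, without limiting it to an arm: "Participants must be willing and able to be contacted regularly by the CM via telephone and to participate in a written survey". Selection is by the practice: "Every participating GP is asked to screen his or her patients according to set inclusion and exclusion criteria". On timing: "Before GPs apply the PHQ-9 questionnaire, potential participants receive oral and written information about the study".
- **Strategy to guarantee the targeted sample size** describes the control condition as "treatment as usual (as agreed on with their GP without involvement of a CM and MHS".
- **Blinding** states that "patients in the intervention and control groups only receive information pertaining to their respective study arm so that each group is unaware of the condition", meaning what patients in the opposite arm receive.
- **Randomization** is at practice level and starts from the GP's consent, not the patient's: "after obtaining written consent from participating GPs, a research assistant generates a pseudonymized code for each practice". The section also says that allocation stays hidden from research staff, GPs and CMs until the intervention is activated. It does not say whether activation comes before or after patients are enrolled.
- **Training of GermanIMPACT care providers** says of the GPs: "Before the inclusion of the first patient, they are personally introduced to the CM assigned to their office".

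**The concern.** The willingness part of the criterion presupposes that the patient has been told about a CM who will telephone regularly. That can happen in an intervention practice. In a control practice there is no CM, and mentioning one would reveal the other arm's condition.

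A patient who does not want such calls would then be ineligible in an intervention practice, while a like patient in a control practice would be enrolled. Because practices are already randomised, this is selection after randomisation. It removes likely non-adherers from one arm before the intention-to-treat population is formed. Willingness to engage may plausibly go with motivation, frailty and questionnaire return, so remission and loss to follow-up could differ between arms without any treatment effect. The Statistical analysis section names baseline symptom severity as the covariate, and adjusting for it would not remove selection on willingness.

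**Working it through.** The plan gives no figure on this point, so there is none to reproduce. The check is a side-by-side reading followed by an illustration of size.

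**Step 1. Split the criterion into its parts.**

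| Part | Intervention practice | Control practice |
|---|---|---|
| Able to be contacted by telephone | Can be judged | Can be judged without mentioning a CM |
| Willing to complete a written survey | Can be asked | Can be asked |
| Willing to be called regularly by the CM | Can be asked | No CM exists; asking discloses the other arm's condition |

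Only the third part depends on the arm.

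**Step 2. Fix the order of events.** The GP consents and the practice is randomised (Randomization). The GP meets the assigned CM before the first inclusion (Training of GermanIMPACT care providers). Patients are informed before the PHQ-9 screen, and consent forms are then signed (Recruitment of patients). Since control practices have no CM, the introduction shows the GP the arm before any patient is selected. The third part is therefore applied after allocation, by someone who in effect knows it.

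**Step 3. Illustrate the size.** Let *u* be the share of otherwise eligible patients who would refuse CM calls, and *k* the remission rate of refusers divided by that of the willing. Neither is in the documents; both are assumed. Control remission is taken as 8.3% (Sample size section). Suppose refusers enter the control arm only and treatment has no effect. The remission rate among the willing, *p_w*, then satisfies

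8.3 = *p_w* × [(1 − *u*) + *u k*], and the spurious difference is *p_w* − 8.3.

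| *u* | *k* | *p_w* (%) | Difference (points) |
|---|---|---|---|
| 0.1 | 0.5 | 8.3 / 0.95 = 8.74 | +0.44 |
| 0.3 | 0.25 | 8.3 / 0.775 = 10.71 | +2.41 |
| 0.1 | 1.5 | 8.3 / 1.05 = 7.90 | -0.40 |
| 0.3 | 2 | 8.3 / 1.3 = 6.38 | -1.92 |

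The planned difference is 25.0 − 8.3 = 16.7 points.

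**Step 4. Effect on the type I error, for one shift in that range.** Take the plan's 250 analysed patients and design effect of 1.46. The effective size is 250 / 1.46 / 2 = 85.6 per arm. Suppose selection alone moved the intervention arm from 8.3% to 10%. For a two-sided pooled z-test at 5%:

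- Pooled rate 0.0915; null standard error √(2 × 0.0915 × 0.9085 / 85.6) = 0.0441.
- Standard error at the shifted rates √((0.10 × 0.90 + 0.083 × 0.917) / 85.6) = 0.0441.
- Rejection probability about 6.7% instead of 5%.

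**The case against.** **One rule on paper.** A reader might infer that the two arms have different eligibility rules. The documents do not say that. The sentence covers all participants, and nothing tells control GPs to waive it. The asymmetry lies in how one part can be applied. A reader might also infer that a patient with, say, hearing loss is barred from one arm only. That does not follow, because ability to use the telephone can be judged in either arm.

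**Concealment.** The Randomization section says that allocation is hidden until activation, and under Warm hand-off the CM appointment follows inclusion. If activation came after all of a practice's patients had consented, the question could be put to everyone. This is the strongest counter-argument, but it does not settle the matter. The text does not date activation relative to enrolment, and the CM introduction before the first inclusion does not fit late disclosure. Asking every patient about CM calls would also tell control patients of the CM, against the Blinding section.

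**Unseen documents.** The article is condensed and the patient information is not shown, so the exact question put to control patients is unknown. That lowers confidence about practice. It does not reconcile the four sections as printed.

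**Feasibility.** A reader might infer that uptake is overstated because refusers never enter the denominator. The article defines no uptake rate, so this stays a possibility.

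**Size and remedy.** The refusal shares and remission ratios have no source in the documents, and the bias can go either way. The upper values are generous, since some refusers would also fail the survey or telephone part in a control practice. Rewording also leaves self-selection at consent in place if patients are told different things by arm. Both objections stand and limit the conclusion.

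**Conclusion.** The point holds in limited form. The criterion is common to both arms as written, but its willingness-for-CM-calls part cannot be applied in control practices as the plan describes them. Following the plan therefore tends to filter refusers out of the intervention arm alone, after randomisation. The other parts of the criterion are unaffected.

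The documents fix neither the size nor the direction of the bias. The range of about -1.9 to +2.4 points rests on assumed refusal of 10 to 30% and an assumed remission ratio of 0.25 to 2. It is small against 16.7 points and would not by itself explain an effect of that size, but a shift within it would lift the error rate above its nominal level. The conclusion also rests on reading the CM introduction and the arm-specific information as preceding patient consent. The CM introduction supports this directly; the arm-specific information is not dated. The change is worth making, but the documents do not show that the trial is invalid.

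**What to change.** 1. Replace the CM-specific wording with one arm-neutral criterion: the patient is willing and able to be reached by telephone by study staff and to fill in written questionnaires. Both arms need this anyway, because assessors telephone patients in both to recover missing data.
2. Enrol patients in intervention practices who consent to the study but decline CM calls. Analyse them as randomised and count them as non-uptake.
3. Reconcile Randomization, Recruitment of patients, Blinding and Training of GermanIMPACT care providers. State when GPs learn their allocation, and when patients receive arm-specific information, relative to patient consent. Without this, refusers in intervention practices can still select themselves out by declining the study.
4. Record for each patient whether enrolment came before or after the change.

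**Cost.** Some intervention patients will not take up the programme, which slightly dilutes the effect; the Sample size section already expects dilution in the intention-to-treat analysis. Enrolment began in February 2013 and was still in progress (Trial status), so this is an amendment to the criteria and patient information for two ethical review boards. Patients enrolled before and after it will have entered under different wording.
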